## Objectives and Hypotheses

Given the findings that show that the excessive cognitive activity present in patients with insomnia is due to a deficit in the functioning of various cognitive functions related to attention and executive functions, we hypothesize that a systematized training in such functions will act as a catalyst on cortical hyperactivity, limiting rumination, intrusive thoughts and disturbing stimuli, thus improving the quality of sleep. We postulate that insomnia patients will also benefit from a general cognitive performance enhancement when CCT mainly targets cognitive functions.

Therefore, the present study has three main objectives: (1) establish the acceptable sessions’ range to determine the maximum training time before fatigue or other adverse conditions appear; (2) determine the therapeutic efficacy of the intervention, establishing the range of needed training sessions, the tolerability to exercises, and the safety of the activity; and (3) verify that CCT can be a plausible non-pharmacological intervention to improve sleep quality in insomnia individuals.

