After post-test data collection, and prior to statistical analyses, all variables will be checked for normality of distribution, and plots will be visually inspected for asymmetry and kurtosis. Then, descriptive statistics will be obtained to provide an overview of the sociodemographic and clinical characteristics of the participants. To examine intervention effectiveness, the changes in all outcome measures from baseline (pretest) to post-intervention (post-test) will be analyzed. Differences in primary outcomes and secondary outcomes will be analyzed through linear mixed models for repeated measures. Models will assess within and between-group differences before and after the intervention. The Group factor (experimental, control) will be included as an independent variable, together with Time (pre-test at baseline, post-test after the intervention). Sociodemographic factors such as gender and age will be used as moderators. Dependent variables will be sleep quality, insomnia severity, quality of life, cognitive abilities, executive function, depressive symptoms, anxiety symptoms, and worrying. To isolate the variable that better explains the model, a hierarchical regression analysis will be conducted with the sleep quality improvements as the dependent variable and the cognitive improvements as the independent ones. This hierarchical regression analysis will be also useful to evaluate the impact of the adherence to the training in the whole sample of participants, regardless of whether they have effectively completed the intervention or not (i.e., cases of attrition or incomplete sessions). The hierarchical regression analysis with the sleep quality improvement as the dependent variable will follow a stepwise approach in which sociodemographic factors will be added in a first step, the data corresponding to the adherence to the treatment (namely, number and length of the completed sessions) in a second step, and the cognitive data from the BRIEF-A and the Cognitive Assessment Battery CAB™ as a third and final step.

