The phase-I trial will follow a standard 3 + 3 protocol. Consequently, the minimum number of participants will be three, and the maximum number of participants will depend on the results of each of the 3-patient cohorts. The phase-II trial will include 20 insomnia patients. Finally, the phase-III trial will consist of a minimum sample size set at 60 participants per group, given that the purpose of this research is to make a first approach to the positive impact of a cognitive training of executive functions on insomnia and to be able to generalize the results obtained with a 95% confidence interval and sufficient statistical power to test hypotheses (sig. bilateral). While a larger number of participants would be desirable for a phase-III trial, it should be considered that the specific selection criteria of the sample and the restricted number of patients that are available at the hospital and the associated centers make it difficult to increase the sample size to account for potential attrition rates and lack of adherence.

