#### Primary Outcome Measures

##### Sleep Quality

The Pittsburgh Sleep Quality Index (PSQI) will be used. The PSQI is a self-report questionnaire that assesses sleep quality and consists of 19 individual items, creating seven components that produce one global score. It takes 5–10 min to complete. The PSQI includes a scoring key for calculating a patient’s seven sub-scores, each of which can range from 0 to 3. The sub-scores are tallied, yielding a global score that can range from 0 to 21. A global score of five or more indicates poor sleep quality, and the higher the score is, the worse the sleep quality can be considered.

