##### Insomnia Severity

The Insomnia Severity Index (ISI) will be used. The ISI is a brief instrument designed to assess the severity of both nighttime and daytime components of insomnia. It comprises seven items assessing the perceived severity of difficulties initiating sleep, staying asleep, early morning awakenings, satisfaction with current sleep pattern, interference with daily functioning, noticeability of impairment attributed to the sleep problem, and degree of distress or concern caused by the sleep problem. Possible scores range from 0 (no clinically significant insomnia) to 28 (clinical severe insomnia).

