##### Quality of Life

The Measuring Quality of Life | The World Health Organization–abridged version (WHOQOL-BREF) will be used. The WHOQOL-BREF is a generic questionnaire to measure the quality of life created by the Study Group on Quality of Life of the World Health Organization. It has two general questions on the quality of life and satisfaction with the state health, and 24 questions grouped into four areas or domains: Physical Health, Psychological Health, Social Relations, and Environment. The measure is calculated by summing the scores in the questions corresponding to each domain and then transforming them to a 0–100 point interval. Possible scores for each domain range from 0 (poor perceived quality of life) to 100 (greater perceived quality of life).

Additionally, the short version of the self-perceived global physical and mental health scale from the Patient-Reported Outcomes Measurement Information System (PROMIS v.1.2; see (Hays et al., 2015, 2017), will be also used. Participants will respond to the following questions: *In general, how would you rate your health?* (Options: Excellent, Very Good, Good, Fair, Poor); *In general, how would you rate your physical health?* (Options: Excellent, Very Good, Good, Fair, Poor); *To what extent are you able to carry out your everyday physical activities such as walking, climbing stairs, carrying groceries, or moving a chair?* (Options: Completely, Mostly, Moderately, A little, Not at all); *In general, how would you rate your mental health, including your mood and your ability to think?* (Options: Excellent, Very Good, Good, Fair, Poor); *In general, how would you rate your satisfaction with your social activities and relationships?* (Options: Excellent, Very Good, Good, Fair, Poor).

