## Expected Results

We expect results to show between-group significant improvements for the cognitive stimulation training group (namely, the experimental group completing the CCT intervention) on sleep quality, quality of life, and cognitive performance. Moreover, due to the relationship between cognitive performance—mainly of cognitive functions—and cognitive awareness and distraction avoidance, we also anticipate a reduction in depressive and anxiety symptoms, and cognitive worrying, all of these linked to a reduced insomnia severity. The fact of receiving the treatment could cause minor improvement in the active control group. Being immersed in the intervention program and carrying out the proposed activities daily—even if they are not designed for it—could lead to an improvement in cognitive functioning. However, if it were to occur, it would not be expected that this improvement would be significant, or if it were, it would be expected to occur in cognitive functions not related to the pathology under study (i.e., verbal fluency).

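### Phase III lists three unranked primary outcome domains and fixes neither a lead outcome nor a success criterion

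*Protocol article*

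**What the plan says.** Under Primary Outcome Measures the article has three subsections of equal standing:

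- Sleep Quality: "The Pittsburgh Sleep Quality Index (PSQI) will be used", with one global score from 0 to 21.
- Insomnia Severity: "The Insomnia Severity Index (ISI) will be used", with one total from 0 to 28.
- Quality of Life: WHOQOL-BREF, scored in four domains with no overall total described ("Possible scores for each domain range from 0 (poor perceived quality of life) to 100"), plus the PROMIS global health questions.

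The Phase III section applies one method to the whole set: "Differences in primary outcomes and secondary outcomes will be analyzed through linear mixed models for repeated measures". Its list of dependent variables puts the three primary domains first, followed by the five secondary ones, with no distinction between them. The sample-size section states that "the phase-III trial will consist of a minimum sample size set at 60 participants per group" and gives as its inferential basis the wish to "generalize the results obtained with a 95% confidence interval and sufficient statistical power to test hypotheses (sig. bilateral"). It attaches the 60 per group to no outcome.

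**The concern.** A confirmatory trial needs a rule, written down before the data are seen, for which result makes it positive. Here the rule could be PSQI alone, any one of the three domains, or all of them, and the article does not choose.

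The rest of the article does not settle it, because its emphasis shifts:

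- Objective 3 speaks only of sleep quality: "verify that CCT can be a plausible non-pharmacological intervention to improve sleep quality in insomnia individuals".
- The hierarchical regression also takes only sleep quality improvement as its dependent variable.
- Expected Results anticipates "between-group significant improvements for the cognitive stimulation training group" in sleep quality, quality of life and cognitive performance. The last of these is a secondary outcome. Insomnia severity, a primary outcome, appears there only as something to which the mood and worry changes are linked.

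Two things are at stake. The headline outcome could be picked after the results are known. And if any single significant primary score were enough, the 5% two-sided level would not apply to the trial's overall claim.

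**Working it through.** **The plan's own figure.** The only design figure is 60 per group. It cannot be reproduced, because no effect size, standard deviation, power or target outcome is given. For orientation, the standardised difference detectable with 80% power at two-sided 5% is d = (1.960 + 0.842) × √(2/60) = 0.51.

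**Number of primary tests.**
- At the level of the Phase III list of dependent variables: sleep quality, insomnia severity, quality of life = 3.
- At the level of the scores described under Primary Outcome Measures: PSQI 1 + ISI 1 + WHOQOL-BREF domains 4 + PROMIS at least 1 = 7.

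**Level per test.** Two-sided 0.05, implied by the 95% confidence interval and bilateral testing in the sample-size section.

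**Chance of at least one false primary success**, if any one success is enough and there is no true effect on any outcome.

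Independent scores: 1 − 0.95^k.
- k = 3: 1 − 0.95³ = 0.143
- k = 7: 1 − 0.95⁷ = 0.302

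Correlated scores: equicorrelated normal simulation with 1,000,000 draws. The correlations are assumptions.

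| Correlation | 3 scores | 7 scores |
|---|---|---|
| 0.3 | 0.1365 | 0.2720 |
| 0.5 | 0.1253 | 0.2294 |
| 0.7 | 0.1096 | 0.1789 |

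Over correlations from 0 to 0.7 the range is therefore about 11–14% for three scores and about 18–30% for seven. Stronger correlation lowers it further: at 0.8 the values are 9.8% and 14.9%.

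**What the remedies do to power.** Take 60 per group and an illustrative d = 0.5, so that d/√(2/60) = 2.739. Power is Φ(2.739 − z), with z the critical value.
- One primary outcome at 0.05 (z = 1.960): Φ(0.779) = 78%.
- Three domains at 0.05/3 = 0.0167 (z = 2.394): Φ(0.345) = 64%. This is the least favourable step of Holm, so power per domain under Holm lies between 64% and 78%.
- Seven scores at 0.05/7 = 0.0071 (z = 2.690): Φ(0.049) = 52%. The difference detectable with 80% power rises from 0.51 to 0.65.

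**The opposite rule.** If all three domains had to succeed, the false-positive rate would be at most 5%. Power would fall: with d = 0.5 on each and independent scores it is 0.782³ = 48%, and positive correlation would move it up towards 78%.

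**The case against.** The strongest reply is that much of this is silence in a condensed journal article. The Phase III section names a model; it does not say that tests will be unadjusted. Adjustment for multiple testing, and the score analysed within each instrument, are commonly set out in a statistical analysis plan, and none is shown here. This stands. A reader might infer that the trial has no error control, but the article shows only that none is stated.

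A second reply is that the error figures depend on a success rule the article never writes. Expected Results joins its anticipated improvements with an and, which is closer to requiring several successes than to accepting any one. This also stands, and the figures have to be read as conditional.

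Third, the Phase III list treats quality of life as one dependent variable. Describing how WHOQOL-BREF is scored does not make each domain a separate primary test. The three-score figure is thus closer to the analysis text, and the seven-score figure is an upper scenario.

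Fourth, it is tempting to say that the article fixes three conflicting hierarchies of outcomes. It does not. Objective 3 is a general aim, the regression is explanatory, and Expected Results is narrative. The outcome sections give one primary/secondary classification and nothing reclassifies an outcome. What remains is a difference in emphasis.

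None of these replies supplies the missing choice. Which outcome decides a Phase III trial belongs in the protocol. The article does address it, by naming a primary set, and leaves it undecided.

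**Conclusion.** The point holds in a limited form: three primary domains share one analysis method, with no lead outcome and no success criterion fixed. The size is conditional on any one significant result counting as success, each test at two-sided 5%, no true effect anywhere, and correlations of 0 to 0.7. On those terms the chance of a false primary success is about 11–14% with one score per domain and about 18–30% with all seven scores.

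A reader might infer a plain 20–30% error rate for this trial. The documents do not support that as a fact, because the any-one rule, the count of seven tests and the correlations are all assumptions. Under an all-must-succeed rule the error would be controlled and the cost would be power. The article leaves open which of these situations applies, and this is what should be corrected.

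**What to change.** Before unblinding, state the decision rule in one of two ways.

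1. **Single primary outcome.** Name one outcome and test it at two-sided 5%. The PSQI global score fits best, since sleep quality is the aim of Objective 3 and the dependent variable of the regression. Then test ISI, and after it quality of life, in fixed sequence, with Holm across the quality-of-life scores.
2. **Three primary domains.** Define one score for each, including a single quality-of-life score, and apply Holm across the three.

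Under either option, report the other outcomes as estimates with 95% confidence intervals, and bring Expected Results into line with the chosen order.

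No extra data are needed. Under the first option, ISI and quality of life can no longer carry the efficacy claim alone. Under the second, power per domain falls somewhat. That matters because the sample-size section says that enlarging the sample would be difficult.

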## Abstract

Insomnia is a frequent and heightened pathology in the general population of developed countries, and its condition generally leads to health discomfort and performance drop in daily and work-related tasks. As current pharmacological treatments for insomnia do not always seem sufficient to mitigate impairment, contemporary cognitive approaches might shed light on developing complementary therapies for this population. We propose a cognitive stimulation intervention program based on the importance of cognitive abilities as precipitating and maintenance variables of sleep disturbances. A full phase I-II-III clinical trial is proposed in which the first two studies will serve to assess the safety of the intervention and to identify the maximum tolerated time of the computerized cognitive training (phase I) and the minimum effective number of training sessions (phase II) in the absence of adverse events or side effects. Next, a phase-III double-blind randomized controlled trial design will be set. Sixty individuals with insomnia aged 25 to 55 years will enroll in a home-based personalized computerized cognitive stimulation program for a total time of 8 weeks, training 5 days per week. Sixty insomnia patients matched in a variety of factors will constitute the active control group, where the orthogonal activities will not be cognitively demanding. Sleep, cognitive, emotional, and quality of life variables will be measured before and immediately after training. A linear mixed model and hierarchical regression analysis will be used to investigate intervention effects. The results derived from this study will be precious for future research and treatment in cognitive performance and clinical pathologies.

**Clinical Trial Registration:** [https://clinicaltrials.gov/], identifier [NCT05050292].

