Despite the extensive literature that corroborates the effectiveness of CBT-I (Koffel et al., 2015; Trauer et al., 2015; Sato et al., 2019), this therapy presents significant setbacks, including the stigma or reluctance in receiving psychological treatments, the in-person appointments, and the need to be performed by a qualified therapist. Given the shortage of professionals trained in CBT-I, availability is limited, and in most cases, it requires the patient to travel long distances. To avoid these primary accessibility impediment, the standard face-to-face CBT-I intervention was adapted to be administered by telephone, while maintaining adequate effectiveness (Bastien et al., 2004a). Still, the need for a therapist continued limiting access because of the waiting lists, so in recent years CBT-I has been extended and computerized to be administered digitally and *via* online. In this sense, CBT-I has been developed as (1) a support tool for conventional therapy, where the patient has access to teaching material and exercises to be completed at home, (2) an autonomous intervention guide with sporadic support from trained healthcare personnel, and (3) an individualized, unguided, and fully automated intervention—namely self-help intervention. However, even though these digital applications have been shown to be effective in clinical trials (see Seyffert et al., 2016; Luik et al., 2017; for review), the complexity of some tasks in the absence of a therapist and the required self-commitment and self-discipline by the patient compromises treatment adherence, reporting in some clinical studies drop rates over 40% (Vincent and Hameed, 2003; Ong et al., 2008). Together with this, it is also worth noting that the normative rules and rigidity of the sleep restriction component of the CBT-I seems to be counterproductive in some patients, diminishing their motivation and leading to diurnal fatigue and sleepiness (Kyle et al., 2014).

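### The phase III pre/post model, read naturally, estimates a difference in mean change; a baseline-adjusted between-arm contrast would be more precise at no extra data cost

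*Protocol article*

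**What the plan says.** All of this comes from the protocol article.

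- **Measurements.** Phase III has two evaluations, a pretest and a post-test. Participants are randomly assigned to one of two groups.
- **Target.** Effectiveness is examined through the change from pretest to post-test in every outcome, using linear mixed models for repeated measures.
- **Model terms.** "The Group factor (experimental, control) will be included as an independent variable, together with Time (pre-test at baseline, post-test after the intervention"). The models are to look at differences within groups and between groups, before as well as after the intervention.
- **Age and gender.** "Sociodemographic factors such as gender and age will be used as moderators".
- **Sample size.** Under Participant Selection and Sample Sizes, "the phase-III trial will consist of a minimum sample size set at 60 participants per group", described as giving "sufficient statistical power to test hypotheses (sig. bilateral"). No effect size, standard deviation or power value is given. The same paragraph says that the selection criteria and the limited pool of patients "make it difficult to increase the sample size to account for potential attrition rates and lack of adherence".

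The section does not name one between-arm contrast as the test of efficacy, and it does not mention the pretest score as a covariate or a common baseline mean.

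**The concern.** In a randomised trial the two arms have the same expected baseline mean. A model that gives each arm its own baseline mean does not use that fact. With one pretest and one post-test, its Group-by-Time term is the difference between arms in mean change, which carries the full noise of the pretest. Adjusting for the pretest removes only the part of the post-test variation that the pretest predicts, and is never less precise in large samples.

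The cost is lost precision, in a trial whose authors say they cannot readily recruit more patients. Two further choices blur the main result. Within-group differences stand beside between-group ones, although only the latter are protected by randomisation. Age and gender enter as moderators, that is, as interactions with the treatment effect, so no single overall effect is defined unless one is named.

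**Working it through.** **Inputs from the article:** 60 per arm; two measurement times; two-sided testing, with alpha 0.05 inferred from the 95% confidence interval.

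**Assumptions, because the article gives no figure:** equal SD at both times, set to 1; complete data; pre/post correlation rho from 0.3 to 0.7, with 0.8 and 0.9 added to show the range.

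**Step 1. The plan's own figure.** The 60 per arm cannot be reproduced, because no effect size, SD or power is given. By the normal approximation, a standardised difference of 0.5 at 80% power needs 63 per arm, and 0.6 at 90% needs 59. Several sets of inputs would lead to about 60, and none is documented.

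**Step 2. What the model estimates.** Whether the arms differ before the intervention can be assessed only if their baseline means are free. In 150 simulated data sets, a mixed model with free Group, Time and Group-by-Time terms gave a Group-by-Time estimate equal to the difference in mean change (largest gap 3e-15).

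**Step 3. Variance per patient, in units of the squared SD.**

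- Change score: 2(1 − rho)
- Baseline-adjusted: 1 − rho² = (1 − rho)(1 + rho)
- Ratio, adjusted to change: (1 + rho)/2, so the saving is (1 − rho)/2

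**Step 4. Detectable difference at 80% power.** For a two-sample t-test with 60 per arm and SD 1 it is 0.516. Multiply by √[2(1 − rho)] for the change analysis and by √(1 − rho²) for the adjusted one. At rho 0.5 this gives 0.516 × √1.00 = 0.516 and 0.516 × √0.75 = 0.447.

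| Assumed rho | Variance, change | Variance, adjusted | Saving | Detectable, change (SD) | Detectable, adjusted (SD) | Per arm giving the same precision as 60 by change |
|---|---|---|---|---|---|---|
| 0.3 | 1.40 | 0.91 | 35% | 0.61 | 0.49 | 39 |
| 0.5 | 1.00 | 0.75 | 25% | 0.52 | 0.45 | 45 |
| 0.7 | 0.60 | 0.51 | 15% | 0.40 | 0.37 | 51 |
| 0.8 | 0.40 | 0.36 | 10% | 0.33 | 0.31 | 54 |
| 0.9 | 0.20 | 0.19 | 5% | 0.23 | 0.22 | 57 |

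The normal approximation gives 0.511 and 0.443 at rho 0.5, so the method hardly matters. As an illustration, power for an assumed difference of 0.4 SD at rho 0.5 is 58% by change and 71% adjusted.

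**Step 5. Check.** Simulation of 20,000 trials per value of rho, 60 per arm, gave savings of 34.4%, 25.5% and 15.3% at rho 0.3, 0.5 and 0.7. At rho 0.5, a mixed model with Group and Time but a common baseline mean had 0.75 of the free model's variance, and ANCOVA had 0.76. Either recovers the gain.

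**The case against.** The strongest reply is that the article does not fix the detail on which the loss depends. A mixed model with Group and Time can carry a common baseline mean, and then nothing is lost. Such details are often left to a fuller document. This stands in part: the factor structure alone wastes nothing, and a common baseline is not expressly excluded. But the article does say that the target is change from baseline and that group differences will be assessed before the intervention as well as after. That wording points to free baseline means.

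A second reply, that the planned model is valid under randomisation, is correct. This is a matter of precision and not of bias.

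A reader might also infer stronger claims that the documents do not support:

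- **A fixed loss of 15% to 35%.** That range follows only from assuming rho between 0.3 and 0.7. At 0.8 to 0.9 the loss is 10% to 5%.
- **Moderators that ruin the treatment estimate.** If age were entered uncentred and spread uniformly over 25 to 55 (SD 8.66), the standard error of the treatment term would grow by √[1 + (40/8.66)²] = 4.73. That is the effect at age 0. At the mean age of 40 the factor is 1, and nothing says that age is uncentred.
- **Efficacy judged within arms.** Expected Results opens by anticipating between-group improvements. Its remark on significance in the control arm is an expectation, not a decision rule.
- **A matched rather than randomised design.** The Abstract says "Sixty insomnia patients matched in a variety of factors will constitute the active control group", but it also calls phase III a randomised controlled trial, and the Phase III section states random assignment. The word is loose and does not bear on this point.
- **An underpowered trial with 40% loss.** The background on digital CBT-I, "reporting in some clinical studies drop rates over 40" per cent, concerns a different intervention. This trial plans at least two calls a week and monitors adherence. The lack of an attrition allowance is openly disclosed. Without inputs, the claim of sufficient power can be neither confirmed nor refuted.

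**Conclusion.** The point holds as one of efficiency. On the natural reading of the Phase III section, the treatment effect is the difference in mean change, which is unbiased but less precise than a baseline-adjusted contrast. The variance saving is (1 − rho)/2. It is largest if the pre/post correlation is modest and small if the correlation is 0.8 or more, and the documents do not say which applies. At rho 0.5 with 60 per arm, adjustment is worth about 0.07 SD in the detectable difference (0.52 to 0.45), and 45 adjusted patients per arm would match 60 analysed by change. These figures assume equal SDs at the two times, complete data and two-sided alpha of 0.05. Because the authors describe enlargement as difficult, precision from data already collected should be used.

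**What to change.** In the Phase III analysis text:

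1. For each primary outcome, name the efficacy estimate as the between-arm difference at post-test. Obtain it from ANCOVA on the baseline score or from a mixed model with a common baseline mean for both arms, in all randomised participants.
2. Enter age and gender as covariates in that model.
3. Report moderation by age and gender in separate models labelled exploratory.
4. Present within-group changes as descriptive only.
5. If a precision gain is quoted, give it as (1 − rho)/2 and state the assumed rho.

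The cost is a change of wording. No new data, visits or patients are needed, and the planned mixed-model framework can be kept.
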